***VI.3. Power calculations***

**Our power calculations suggest that we will need to enroll ~750 subjects.** Based on our own multi-ethnic data, we have estimated a minor allele frequency of 0.32 for the risk T allele at rs7903146 *TCF7L2* and 0.35 for the risk K allele at *KCNJ11* E23K. Assuming Hardy-Weinberg equilibrium, the proportion of subjects carrying the risk homozygous genotype at either locus will be ~10% and ~12% respectively. With the difference in insulinogenic index between CC and TT homozygotes at rs7903146 *TCF7L2* documented by Saxena *et al.,* (see Section C.3 above), 750 subjects should provide >80% power to detect the same difference at a one-sided alpha of 0.05. Similarly, assuming that the difference in insulin sensitivity after one year of metformin treatment by E23K genotype is also detectable in the acute setting, 750 subjects provide >90% power at the same one-sided alpha of 0.05 (73% for a two-sided test). With regard to the sulfonylurea challenge, this sample size has >99% power to detect a 10% difference in trough glucose between genotypic groups at a one-sided alpha of 0.05, and 94% power to detect a 20% difference in peak insulin at a one-sided alpha of 0.05.

While these power calculations apply to a study population of a single ethnic group, expanding our study to include a multi-ethnic population would require enrollment of ~1,000 subjects.

1. **Risks and DIscomforts**

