***VI.2. Statistical analysis***

**Non-normal variables will be log transformed.** They will be adjusted for age, gender and BMI, and residuals will be compared between each group of homozygous individuals at each locus by Student t tests. Since these polymorphisms may influence glycemic traits by affecting BMI, both BMI-adjusted and unadjusted analyses will be reported. Secondary analyses will include exploration of genetic models (dominant, recessive or additive), by including heterozygous individuals and performing ANOVA across the three genotypic groups, with subsequent Bonferroni adjustment for multiple comparisons. The role of self-reported ethnicity will be evaluated with an interaction term; analyses will also be repeated within each self-reported ethnic group, and in the aggregate of groups where minor allele frequencies are comparable. As these experiments involve validation of previous hypotheses, nominal *P* values below 0.05 will be considered statistically significant.

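### The one-sided (>90%) and two-sided (73%) power figures for Aim 2 do not fit together at alpha 0.05, and the other headline powers are given one-sided only

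*Protocol*

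**What the plan says.** Section VI.3 of the protocol states the target as "Our power calculations suggest that we will need to enroll ~750 subjects". For Aim 2 the effect is set by "assuming that the difference in insulin sensitivity after one year of metformin treatment by E23K genotype is also detectable in the acute setting", and the resulting power is given as "750 subjects provide >90% power at the same one-sided alpha of 0.05 (73% for a two-sided test". No separate alpha is given for the two-sided figure.

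The other three headline powers are also at one-sided 0.05, with no two-sided counterpart:

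- Insulinogenic index by *TCF7L2* genotype: "750 subjects should provide >80% power to detect the same difference at a one-sided alpha of 0.05".
- Trough glucose: ">99% power to detect a 10% difference in trough glucose between genotypic groups at a one-sided alpha of 0.05".
- Peak insulin: "94% power to detect a 20% difference in peak insulin at a one-sided alpha of 0.05".

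Section VI.2 specifies Student t tests between the two homozygous groups, with ANOVA across three genotypes as secondary, and says that "nominal *P* values below 0.05 will be considered statistically significant". It does not say whether tests are one-sided or two-sided.

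Section VI.3 closes by putting the requirement for a multi-ethnic population at about 1,000, and Section VII.1 gives 1,000 as the number to be enrolled.

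**The concern.** One-sided and two-sided power for the same comparison, sample and effect are tied together: either one determines the other. A drop from above 90% to 73% is larger than moving from a one-sided to a two-sided 5% test can produce, so at least one figure is wrong or rests on an input that is not stated.

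These figures are the stated basis for about 750 subjects and the starting point for 1,000. If 73% is right, the one-sided headline for Aim 2 is overstated by at least 8 points. If the headline is right, two-sided power is understated by at least 10 points. A reader cannot tell which.

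A second, smaller matter is that the headline powers are all one-sided while Section VI.2 adopts no one-sided rule. A P value below 0.05 from a t test is conventionally read as two-sided, and on that reading only Aim 2 has a power figure for the test that would be reported.

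**Working it through.** **Inputs.** N = 750, the two Aim 2 powers and the three other powers come from Section VI.3. The allele frequency there is "0.35 for the risk K allele at *KCNJ11* E23K". Under Hardy-Weinberg equilibrium this gives 750 × 0.35² ≈ 92 KK and 750 × 0.65² ≈ 317 EE subjects, so 92 + 317 − 2 = 407 degrees of freedom. The two-sided alpha is taken as 0.05, which is an assumption.

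**Reproducing the stated figure.** The available text gives no numerical Aim 2 difference or SD, so neither power can be rebuilt from an effect size. The pair can still be tested against itself, because the unknown effect and SD enter both powers only through the noncentrality

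λ = (δ/σ) / √(1/n₁ + 1/n₂),

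with one-sided power ≈ Φ(λ − 1.645) and two-sided power ≈ Φ(λ − 1.960).

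**Starting from 90% one-sided.** λ = 1.645 + 1.282 = 2.926 (unrounded quantiles). Two-sided power = Φ(2.926 − 1.960) = 83.3%. Since the protocol says more than 90%, the two-sided value would be higher still.

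**Starting from 73% two-sided.** λ = 1.960 + 0.613 = 2.573. One-sided power = Φ(2.573 − 1.645) = 82.3%. If 73% is a rounding of anything from 72.5% to 73.5%, the range is 81.9% to 82.7%.

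**Sensitivity to the approximation.** The noncentral t at 407 df gives 83.3% and 82.4%. At only 10 df the values are 81.0% and 84.3%, so the conflict remains.

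**Largest possible gap.** The difference Φ(λ − 1.645) − Φ(λ − 1.960) is greatest midway, at λ ≈ 1.80, where it equals 2Φ(0.1575) − 1 ≈ 12.5 points. The stated gap exceeds 90 − 73 = 17 points. Under this approximation, no effect size, SD or allele frequency shared by the two figures can produce it at 0.05.

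**What would reconcile the pair.** Any one of the following would do so, and none is stated for these figures:

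- a two-sided alpha of about 0.021;
- a one-sided alpha of about 0.098;
- different sample sizes: (2.573/2.926)² = 0.773, so 73% at about 580 with 90% at 750, or 73% at 750 with 90% at about 970.

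**At 1,000 subjects.** Starting from the lower figure, λ = 2.573 × √(1000/750) = 2.971. Two-sided power is Φ(1.011) ≈ 84% and one-sided power is Φ(1.326) ≈ 91%, with effect, SD and genotype proportions unchanged.

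**Two-sided counterparts of the other headline powers**, from Φ(z(power) + 1.645 − 1.960):

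| Endpoint | Stated, one-sided | Two-sided |
| --- | --- | --- |
| Insulinogenic index | >80% | >70.1% |
| Trough glucose | >99% | >97.8% |
| Peak insulin | 94% | 89.2% |

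The first two rows convert lower bounds, not estimates.

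**The case against.** The arithmetic assumes a two-sided alpha of 0.05 that the protocol does not print. That stands as a condition, although 0.05 is the only level given in Sections VI.2 and VI.3 and the natural reading.

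A reader might infer three stronger points that the document does not support.

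*That Section VI.2 contradicts the one-sided power calculations.* It does not: it is silent on sidedness, which may be settled in an analysis plan that is not shown. The Specific Aims give directional hypotheses for Aim 2 (less improvement in insulin sensitivity) and Aim 3 (lower insulinogenic index and GLP-1), and Section VI.2 presents the work as validating earlier hypotheses. The newly discovered variants have no such direction, but no power is claimed for them.

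*That Aim 2, or the study, is undersized.* A shortfall below 80% follows only if 73% is the correct figure, the test is two-sided and N is 750. The plan is to enrol 1,000. Ethnic heterogeneity may use up some of the gain, since Section VI.3 ties its calculations to a single ethnic group, but the document does not establish a shortfall.

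*That Aim 3 falls below 80%.* The stated figure is a floor, and converting a floor says only what is guaranteed.

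The near match between 91% one-sided at 1,000 and 73% two-sided at 750 might suggest a slip over N. That is conjecture, because the text attributes both figures to 750. It is also fair to note that the protocol prints the less favourable 73% openly.

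**Conclusion.** The Aim 2 pair is internally inconsistent if both figures use alpha 0.05. The mismatch is at least 10 points on the two-sided side if the headline is right, or at least about 8 points on the one-sided side if 73% is right. This conclusion does not depend on the missing effect size or SD. It assumes only that the two figures share N, effect and SD, as the sentence says, and that the two-sided alpha is 0.05. Which figure is wrong cannot be determined from the document.

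The one-sided basis of the other three headline powers is a reporting gap, not a contradiction. The point should be fixed because wrong power figures support the enrolment target, but it is not evidence that the target itself is wrong.

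**What to change.** In Section VI.3:

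1. Recompute Aim 2 power from the insulin sensitivity means and SDs that were used. Correct the wrong figure, or state the different N or alpha behind it.
2. Give Aim 2 power at the planned enrolment of 1,000 as well as at 750.
3. Report two-sided power beside each one-sided figure, as is already done for Aim 2. Peak insulin becomes about 89%. The insulinogenic index and trough glucose need fresh calculation, because their stated floors guarantee only about 70% and 98%.

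This makes the stated powers match whichever test is reported. It costs a few sentences and a short recalculation, and changes no endpoint, procedure or test. The drawback is that some stated powers will look less favourable.

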***VII.1. Risks to the subjects and implementation of safeguards***

**We will enroll 1,000 male or non-pregnant female adults with early type 2 diabetes (on diet treatment only).** No vulnerable populations will be enrolled. Although glipizide is labeled as a pregnancy Class C drug and metformin as a Class B drug, no pregnant or nursing women will be enrolled; in part, this is due to the known alterations in glycemic physiology during pregnancy. Women at risk of being pregnant (i.e. sexually active without adequate birth control) will receive a urine pregnancy test before enrollment.

**In order to avoid an exaggerated response to either of the two study medications, we will exclude subjects with impaired renal or hepatic function.** This will be initially determined by both history and examination of the medical record, which will be available to us due to our exclusive use of the Partners-specific source database. Renal dysfunction will be defined as a decrease in estimated GFR < 60 ml/min/1.73 m^2^, based on the most recent serum creatinine measurement available in the electronic medical record (within the past year), and calculated by the Modification of Diet in Renal Disease equation ([81](#_ENREF_81)). Subjects with advanced diabetes (i.e. on antidiabetic medications), type 1 diabetes (i.e. on insulin therapy) or suspected Maturity Onset Diabetes of the Young (based on age at diagnosis and familial transmission) will also be excluded. Finally, subjects with a history of porphyria or severe sulfonamide allergy will be excluded to avoid potential hypersensitivity reactions to glipizide.

**In order to prevent the rare potential complication of *lactic acidosis* in subjects with impaired renal function who receive metformin, we will recalculate GFR based on a current serum creatinine level.** A serum creatinine level will be measured on Day 1, and current GFR will be estimated by the Modification of Diet in Renal Disease equation ([81](#_ENREF_81)). Because subjects with GFR < 60 ml/min/1.73 m^2^ (based on a recent historical creatinine measurement) will have been excluded from enrollment, we expect that only a few subjects will meet this definition after enrollment. These subjects will be able to complete the sulfonylurea challenge (as glipizide does not require dose adjustment based on renal function), but will not receive metformin for the second phase of this study (due to begin on Day 6): instead, they will undergo a simple OGTT on Day 8 in the absence of any metformin treatment. In addition, if they are being treated with diuretic therapy we will make sure their doses are stable throughout the study. Likewise, we will be performing an ALT/AST measurement, and if the result is 3x higher than the upper limit of normal the subject will not take the metformin, and instead report for a simple OGTT. As a further precaution, any subject with a planned radiologic or angiographic study requiring IV contrast within one week of completion of this study will also be excluded from metformin treatment, because iodinated contrast may precipitate the acute alteration of renal function, and this might lead to metformin accumulation and resulting lactic acidosis. Finally, subjects will also be instructed to limit their alcohol intake to one drink or less on the night preceding their second visit while on active metformin therapy.

**After these exclusion criteria are implemented, the risks to the subjects will be minor.** These include 1) hypoglycemia, 2) blood drawing, 3) gastrointestinal side effects due to metformin, 4) stress from a potential diagnosis of pre-diabetes or diabetes and 5) loss of confidentiality. We will address these sequentially.

- - 1. **During the sulfonylurea challenge, subjects are expected to become hypoglycemic.** The degree of hypoglycemia may be blunted in our population at risk of diabetes, for whom some amount of insulin resistance is likely to be present. In addition to the exclusion of subjects with impaired renal or hepatic function (in whom duration of action may be more pronounced), we will take the following precautions to avoid complications of severe hypoglycemia: 1) exclusion of subjects with a fasting fingerstick < 80 mg/dl, 2) selection of a low dose of glipizide, 3) close monitoring of subjects for the appearance of hypoglycemic signs and symptoms (diaphoresis, nervousness, jitteriness, shakiness, confusion, blurred vision, lightheadedness, slurred speech), 4) rapid fingerstick measurement if any of the above are noted, 5) half-hourly fingerstick glucose measurements even in the absence of symptoms, 6) increase in the frequency of fingerstick measurements (even when asymptomatic) if these drop below 50 mg/dl, and 7) termination of the challenge with juice and a glucotab if the fingerstick is <50 mg/dl (with symptoms) or <45 mg/dl (without symptoms), with indications that the subject break his/her fast immediately. We will also have IV dextrose on standby, and will provide all subjects with a carbohydrate-rich meal at the conclusion of the challenge. Metformin only causes hypoglycemia when used in combination with other hypoglycemic agents; in order to avoid this eventuality we have established a safe washout period. Even with the conservative estimation of prolonged glipizide half-life in the elderly (~10h), a total of 12 half-lives will have transpired between Day 1 and Day 6, essentially eliminating any chance of both drugs interacting in any subject.
    2. **Blood drawing will be minimal and spread out over one week.** On Day 1, blood work will involve baseline measurements (35.5 cc), DNA 20 cc, two time points with 22cc of blood and four time points with 17cc of blood each, for a total of 167.5 cc of blood (~11.3 tablespoons). On Day 8, blood work will involve a baseline measurement of 27 cc, two time points with 22cc of blood, one time point~~s~~ with 17cc and three time points with 10cc. This totals 118cc (~8.0 tablespoons) of blood taken during Day 8 and 285.5cc (~.3 tablespoons) for both days. A 20G intravenous catheter will be placed in the antecubital vein each day, in order to minimize the discomfort of repeated venipuncture. Occasionally a bruise may be produced; rarely, infiltration of the catheter with a resulting local skin reaction may also occur. Some subjects may experience syncope due to catheter insertion.
    3. **Metformin may cause loose stools or overt diarrhea.** In order to minimize this side effect, which occurs in ~15% of subjects, we have elected to use the lowest single dose used clinically (500 mg) and limit it to four doses only. If diarrhea becomes intolerable the subject may elect to discontinue metformin, and will undergo a simple OGTT on Day 8 instead.
    4. **Subjects with previously undiagnosed pre-diabetes or diabetes may have results consistent with either of these diagnoses.** As the study is targeted toward individuals at risk of developing diabetes, this eventuality will be prominently discussed during the informed consent process. A fasting glucose between 100 and 125 mg/dl in either visit (indicating impaired fasting glucose) or a 2h OGTT between 140 and 200 mg/dl (indicating impaired glucose tolerance) would be suggestive of pre-diabetes. A fasting glucose ≥ 126 mg/dl in either visit or 2h OGTT glucoses ≥ 200 mg/dl would be suggestive of diabetes; because the diagnosis of pre-diabetes or diabetes requires repeat confirmation and the OGTT will be performed under the influence of metformin, this study will not make a definitive diagnosis. Subjects who meet these criteria or who have other laboratory values deemed by the study physicians to be clinically actionable will be informed and asked to follow up with their primary care physician, who may also be notified if the subject agrees. Some of these values are not required as safety measures in our study, but are provided to us by the laboratory because the measurement of study-required creatinine or liver transaminases occurs in a bundle with other electrolytes and liver function tests.  These other incidental laboratory values will include results outside of the following ranges, determined by our study physicians to merit clinical action: sodium 130-150 mmol/L, potassium 3.2-5.2 mmol/L, 8.5-11 mg/dL, or alkaline phosphatase above 300 IU/L. Owing to the above considerations, results will not be entered into the medical record.
    5. **Subject confidentiality will be protected.** In order to protect the privacy of the subjects, we will provide them with a coded, anonymous numerical identifier at enrollment. Anthropomorphic, biochemical, , and genetic data will be linked to this anonymous identifier only, and will not be part of the medical record. The key will be stored in the PI’s office in a locked cabinet and in his password-protected hard drive. Only study personnel who have undergone appropriate human research training and signed standard confidentiality agreements will have access to these data. All subject-related documents will be stored in locked file cabinets within locked offices.

1. **Potential Benefits**

**This study will have no personal direct benefit to subjects, other than provide initial diagnostic tests which may indicate pre-diabetes or the presence of diabetes.** On a societal level, however, this proposal should help clarify the pathophysiologic mechanisms by which these key genetic variants increase risk of type 2 diabetes, and assess their impact on commonly used antidiabetic treatments. In addition, this pilot study will lay the groundwork for a long-term, outcomes-based pharmacogenetic clinical trial.

**A number of genetic variants have already been reproducibly associated with type 2 diabetes; the list is only expected to grow.** It will be crucial to harness this new genetic knowledge so that it can refine our understanding of the pathophysiology of diverse forms of diabetes, enhance our prognostic ability and direct our choice of appropriate therapies. The discovery that some of these polymorphisms have measureable effects on glycemic parameters opens the door to targeted pharmacogenetic studies. The information obtained from pilot experiments such as the ones outlined in this proposal should provide the foundation necessary to design and implement genome-based clinical trials, with the hope that these novel genetic insights will translate into improved medical care and preventive measures for public health.

1. **Monitoring and Quality Assurance**

***IX.1. Data monitoring***

**A Data Safety Monitoring Plan will be implemented.** The PI will review the safety and progress of this study on a monthly basis. At the request of the NIH, the DSMP has been modified to include a Designated Safety Officer not involved in the conduct of the study. [name] of the Diabetes Center at MGH has graciously agreed to perform this function, and will meet with the PI and the Research Coordinator on a quarterly basis to monitor subject safety. In addition, the PI will include results of the review in the annual progress reports submitted to the clinical research center, IRB, and NIDDK. The annual report will include a list of adverse events. It will address: (1) whether adverse event rates are consistent with pre-study assumptions; (2) reason for dropouts from the study; (3) whether all participants met entry criteria; (4) whether continuation of the study is justified on the basis that additional data are needed to accomplish the stated aims of the study; and (5) conditions whereby the study might be terminated prematurely. Finally, the research review committee at the clinical research center will review each protocol annually for safety.

***IX.2. Adverse events***

**IX.2.a. Adverse event grading**

1. Attribution scale. An adverse event is defined as both an expected side effect that is of a serious nature, or an unexpected side effect/event regardless of severity. All events will be graded as to their attribution (unlikely, possibly, probably, or definitely related to protocol) and their severity (mild, moderate or severe). **Severe or serious** adverse events are events that result in death, a life threatening experience, hospitalization, persistent or significant disability, a congenital birth defect or a medical intervention designed to prevent any of the above; **moderate** adverse events cause discomfort enough to interfere with usual activities, are persistent and/or require medical evaluation and treatment; **mild** adverse events involve the awareness of signs and symptoms that are easily tolerated, cause no loss of time from normal activities, do not require medical evaluation and/or treatment, and are transient. Any event that is reported to either the PI or his designated research associates by the subject or medical staff caring for the subject and which meets the criteria will be documented as such.
2. Expected risks. As detailed in the protocol and consent form, the expected risks include:

- Hypoglycemia during sulfonylurea challenge
- Blood drawing and intravenous catheter insertion
- Gastrointestinal side effects due to metformin
- Stress from a potential diagnosis of diabetes, and
- Loss of confidentiality.

**IX.2.b. Plan for reporting both anticipated and unanticipated adverse events**

**Each subject is evaluated for any adverse events.** Any event that is reported to either the PI or his designated research associates by the subject or medical staff caring for the subject and which meets the criteria will be documented as such. Any event that is reported will then generate an adverse event report, which will be submitted to the IRB and the clinical research center. The report will include a description of the event, when and how it was reported, as well as any official chart records or documentation to corroborate the event or the reporting of the event.

**Any severe and/or unanticipated adverse event will be immediately reported to the IRB and the clinical research center.** All other adverse events will be reported in a timely fashion to the IRB and the clinical research center, preferably within 2 weeks of the date of the event. All adverse events will be summarized annually and submitted to the IRB and the clinical research center. Any action resulting in a temporary or permanent suspension of this study (e.g. FDA actions, IRB actions, or actions by a commercial sponsor or by the investigators or co-investigators) will be reported to the appropriate NIDDK program official.

